### Participant recruitment

To reach the target sample size efficiently, we will implement a focused recruitment strategy. Potential participants will be identified through electronic medical records at the participating clinics and approached during their regular visits. We will also use posters in waiting areas and collaborate with treating physicians for referrals.

### Intervention protocol

#### The control group: receive routine education and a hand book.

The control group will receive routine foot care education, which reflects the current standard of care in the participating clinical settings. During hospitalization, the nurses will conduct health education for patients. The content of health education will include daily self-care knowledge, such as regular exercise, blood glucose monitoring, medication, prevention and treatment of complications, foot care, etc. All patients will receive the Foot Care Guidance for Diabetic Patients handbook. It is developed referring to the domestic and international guidelines for diabetic foot prevention and management [32–34]. The handbook contains 3 parts regarding foot care for diabetic patients: the definition of diabetic foot (DF), the manifestation of DF, and the method of daily foot care.

Upon hospital discharge, the nurses will inform patients of precautions when leaving the hospital, instruct them on medication-taking methods, emphasize the importance of self-care at home, educate them to pay attention to healthy eating, regular exercise, taking medicine as prescribed by the doctor, strengthening daily foot care, advise patients to seek medical attention promptly if their condition worsens or they experience any unusual discomfort at home.

After a patient discharge, the nurses will follow up with the patient via telephone once a month, for a total of 4 follow-up telephone interviews. The follow-up will include assessing the patient’s blood glucose control and foot care. Additionally, the research team will provide guidance on disease-related issues the patient encountered at home.

#### The intervention group: receive MTM-based foot-care education.

When a patient is admitted to hospital, they will receive the same routine nursing as the control group. In addition, they will be invited to participate in the MTM-based foot-care education program.

### Participatory dialogue

Participatory dialogue will be developed through one-on-one face-to-face communication. On day 1–3 of admission, one-on-one communication will be conducted by a trained senior nurse. We will initiate discussions by encouraging patients to share their routine practices of examining their feet. Patients will be prompted to describe their understanding of their current foot condition, and they will be asked to detail the specific preventive foot care practices they have independently implemented. Based on the knowledge of the patients’ condition and education, the nurses will explain the clinical manifestations and severity of DF, consequences of DF, the disadvantages of delayed medical treatment. The duration of each education session will be 10–20 minutes, using the *Foot Care Guidance for Diabetic Patients* handbook to complete the explanation. To further improve the patient’s cognition of DF, the nurses will discuss the benefits as well as barriers of foot care with the participants.

### Behavioral confidence

For the “behavioral confidence” construct, health education lectures will be held by the research team who have been specifically trained. The education session will be delivered to participants with PowerPoint and video presentation for about one hour in the clinical ward, along with their family members or carers. On days 4–7 of admission, the nurses will demonstrate and instruct the patients on proper foot care. The ‘teach-back’ method will be introduced to improve the patients’ comprehension [35].

### Changes in the physical environment

Regarding “Changes in the physical environment”, we will provide participants with a bag of foot-care supplies, which includes a cotton towel, a pair of pressure-relief insoles, an infrared thermometer, a toenail file and samples of Vaseline. These supplies are all necessary for foot care. The research nurse will provide verbal persuasion as she shows the patient each item of foot care supplies and review the purpose of each.

In addition, we will also develop a mobile application (app) to provide a software support system for the patients. The smartphone app for diabetes management (register number: 2018SR446465) consists of 4 modules: syndrome differentiation, body differentiation and health preservation, thesaurus, and interactive follow-up. Patients in the intervention group will be required to install the software before hospital discharge. In addition, the research nurses will teach the participants to use the app correctly and ensure that they can use it by themselves.

### Emotional transformation

The intervention features a multi-sensory simulation of the DF experience, which aligns with the MTM’s “emotional transformation” framework. Participants will undergo a standardized protocol where a 2 kg sandbag is attached to their ankles to mimic symptoms of lower extremity arterial disease, and sponge platforms will be used to induce neuropathic sensory differences. This immersive activity is designed to promote emotional engagement with potential foot complications.

Post-discharge support will be sustained via a dedicated WeChat platform, including: 1) a public account for structured educational content, and 2) a communication group for peer interaction and consultation with the research team. Additional one-to-one follow-ups will provide personalized psychological support and address individual patient concerns. The specific content pushed via the WeChat public account is detailed in Table 1.

**Table 1 pone.0350892.t001:** Overview of the foot-care education program.

Module		Time	Methods	Content
**Initiation of Behavior Change**	Participatory Dialogue	Days 1–3 of admission	One-on-one face-to-face communication	1.1 Clinical manifestations and severity of diabetic foot

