### Sample size calculation and allocation

The sample size was calculated using G*Power 3.1 software for a two independent samples t-test. The primary outcome was pre-hospital delay intention (PHDI). A large effect size (Cohen’s d = 0.80) was adopted, which was justified by a previous study in patients with high-risk diabetic foot that reported a large effect size on pre-hospital delay intention [30]. The type I error rate (α) was set at 0.05 (two-tailed), and the statistical power (1 − β) was set at 0.85 [31]. The calculation yielded a required sample size of 30 participants per group. Accounting for an anticipated 15% attrition rate during follow-up, the final target sample size was set at 35 patients per group (total N = 70).

All the participants will be randomly divided into control group (n = 35) and intervention group (n = 35) upon admission. Randomization will be performed automatically by Microsoft Excel at enrollment. The “RAND ()” function in Microsoft Excel will be used to generate a series of random numbers by an independent researcher and kept in a sealed, opaque envelope. These numbers will be served as the basis for patient allocation into either the control group or intervention group.

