				4.1.2 Podiatric symptom experience
		After hospital discharge	Create a WeChat official account Send the tweets to the WeChat group	4.2.1 What is diabetic foot?

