				4.2.10 Nail care and footwear selection
				4.2.11 Seeking medical help
				4.2.12 Blood glucose management
				4.2.13 Nutrition management for diabetes
				4.2.14 Medication management
				4.2.15 Insulin injection
				4.2.16 Physical exercise
				4.2.17 Psychological adjustment
	Practice for Change	After discharge, once a week	Keep a record WeChat contact	5.1 Keep a record on *Foot Care Diary Card*

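### Control patients at the same two hospitals could reach part of the intervention (a WeChat account called public, a lecture on the ward); no barrier or exposure record is described, and the power has little reserve for dilution

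*Protocol article*

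**What the plan says.** The protocol article fixes the following.

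- **Allocation** (Sample size calculation and allocation; Location and setting). Patients are "randomly divided into control group (n = 35) and intervention group (n = 35) upon admission", at two tertiary hospitals. The study timeline gives one recruitment window, February to May 2026, so both arms are inpatients at the same hospitals over the same months.
- **Lecture** (Behavioral confidence). The intervention lecture runs "for about one hour in the clinical ward, along with their family members or carers".
- **Post-discharge content** (Emotional transformation; Table 1). Material goes out through "a public account for structured educational content" and a communication group. Table 1 names the method as "Create a WeChat official account", with posts also sent to the WeChat group. One of its 17 topics is "4.2.11 Seeking medical help".
- **Eligibility** (Participants and eligibility criteria). Patient and caregiver must both be able to use WeChat. This applies to controls too.
- **Nearest safeguard** (Data collection and management). Participants may not join other structured foot-care programmes, and concurrent care is recorded. This does not extend to the trial's own intervention material.
- **Limitations** (Discussion). Contamination is not listed.
- **Sample size**. The calculation uses d = 0.80 in full; attrition is the only allowance added.

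**The concern.** The primary outcome is an intention score, and an intention can be changed by information alone. If some controls read the posts on seeking care, or sit within earshot of the lecture, their scores may move in the same direction as those of the intervention arm and the difference between arms shrinks. The bias is towards no effect.

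Two things are at stake. The sample size was set with almost no slack, so even a modest loss of effect takes power below the stated target. And if nobody records whether controls met the material, a small or null result will be harder to interpret: the team could not say how far leakage might explain it, and that record is difficult to rebuild after the trial.

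**Working it through.** **Inputs from the protocol article (Sample size calculation and allocation).** "The sample size was calculated using G*Power 3.1 software for a two independent samples t-test". "A large effect size (Cohen’s d = 0.80) was adopted". Two-sided alpha 0.05, power 0.85, 30 per arm required, 15% attrition, 35 per arm enrolled.

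**Input not in the document.** The share c of the effect lost to contamination. It is an assumption, shown as a range.

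**Formula.** Two-sample t-test with n per arm: df = 2n − 2, noncentrality = d·√(n/2), and power is the probability that a noncentral t exceeds the two-sided 5% critical value in absolute size.

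**Step 1: reproduce the plan.** With n = 30 and d = 0.80, noncentrality = 0.80 × √15 = 3.10 on 58 df, and power = 0.861. With n = 29, power = 0.849. So 30 is the smallest n that reaches 0.85, and the stated figure is confirmed. After 15% attrition, 35 × 0.85 = 29.75, or about 30 evaluable per arm.

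**Step 2: reserve.** At 30 per arm, power 0.85 needs d = 0.787. Since 1 − 0.787/0.80 is about 1.7%, any larger loss takes power below target. Power 0.80 needs d = 0.736, a loss of about 8%.

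**Step 3: dilution.** Effective d = 0.80 × (1 − c), SD unchanged.

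| Assumed c | Effective d | Power, 30 per arm | Power, 35 per arm |
|---|---|---|---|
| 0 | 0.80 | 0.861 | 0.910 |
| 5% | 0.76 | 0.825 | 0.880 |
| 10% | 0.72 | 0.783 | 0.844 |
| 20% | 0.64 | 0.684 | 0.752 |
| 30% | 0.56 | 0.569 | 0.637 |

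The 35-per-arm column applies only if nobody is lost.

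**Step 4: variant.** Suppose instead that a share c of controls receives the whole effect and the rest none. The control variance becomes 1 + c(1 − c) × 0.64. Power at 30 per arm is then slightly lower: 0.771 at 10% and 0.662 at 20%.

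**Limit of the arithmetic.** These figures follow the plan's own t-test calculation. The planned analysis is a repeated-measures ANOVA, whose power will differ.

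**The case against.** A reader might infer more than the text supports, and the case against those stronger readings is good.

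- **Shared wards.** The article does not say that the arms share wards, rooms or nurses. It gives a place for the lecture, not open attendance.
- **Open access.** "Public" may only name a type of WeChat account, since Table 1 calls it an official account. Posts also go to a group described only for the intervention arm. Nothing says that controls are told of the account or can see it.
- **Content.** Table 1 lists foot-care steps, massage, exercises and precautions for the lecture module. The message about the harm of delay sits in the one-to-one sessions. Overhearing the lecture would therefore not directly convey that message. Among the posts, the care-seeking topic is one of 17, and controls are already advised at discharge to seek help promptly.
- **Size.** The one-to-one dialogue, supplies, taught app, simulation, diary card, weekly contact and home visits are hard for controls to obtain. A 20% or 30% loss would need substantial leakage. The study behind d = 0.80 may already include some contamination; the article does not say.
- **Omission.** Account settings and room use could be covered in a full protocol that is not shown.

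All of this stands against saying that contamination will occur, that the power is lost, or that the sample size is wrong. It does not remove the narrower point. The delivery routes are stated design choices, one of them is labelled public, its topics include one tied to the primary outcome, and the text describes neither separation nor measurement. If access is already restricted, one sentence would settle it.

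**Conclusion.** The point holds as a risk that the design leaves open, not as a demonstrated bias. Contamination could pull the effect on pre-hospital delay intention towards zero. The amount is unknown and probably partial. The sample size is correct on its own inputs but has almost no reserve: at 30 evaluable per arm, a loss of about 2% of the assumed effect is enough to miss 85% power, and about 8% takes it to 80%. The larger losses of power depend wholly on the assumed dilution and are illustrations, not forecasts. The change is worth making because prevention is cheap and exposure that goes unrecorded during the trial is hard to recover later. Cluster randomisation or a larger trial is not called for on this evidence.

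**What to change.** Keep individual randomisation and N = 70.

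1. Deliver the posts only through the invitation-only group, or an account with restricted access, for allocated intervention patients and their carers. State this access rule in the protocol.
2. Hold the lecture and the foot-care demonstrations where control patients are not present.
3. At the final assessment, after the outcome questionnaires and before controls are offered the deferred intervention, ask **both** arms the same brief question on whether they met the programme material. Someone other than the blinded assessor should ask it. Asking controls alone could reveal allocation, and asking at the 4-week visit could prompt them to look for the material.
4. Report exposure by arm descriptively. Exposure arises after randomisation and there are only about 30 to 35 controls, so any analysis by exposure should be labelled supportive.
5. List contamination among the limitations.

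**Cost.** Slightly less convenient scheduling, account or group settings, and one or two added questionnaire items, put by a person other than the assessor. No additional patients are needed.

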				1.2 Consequences of diabetic foot
				1.3 Disadvantages of delayed medical treatment for diabetic foot problems
				1.4 Benefits of foot care
				1.5 Barriers to foot care
	Behavioral Confidence	Days 4–7 of admission	Health education lecture Teach-back method	2.1 Foot care steps
				2.2 Foot massage
				2.3 Foot exercises
				2.4 Foot care precautions
	Changes in the Physical Environment	One day before discharge	Provide foot-care supplies	3.1 Foot-care supplies: a towel, a pair of pressure-relief insole, an infrared thermometer, toenail file, and samples of Vaseline.
			App installation	3.2 App installation and usage support
**Sustenance of Behavior Change**	Emotional Transformation	One day before discharge	Experiential education	4.1.1 Symptom experience of lower extremity arterial disease
				4.1.2 Podiatric symptom experience
		After hospital discharge	Create a WeChat official account Send the tweets to the WeChat group	4.2.1 What is diabetic foot?
				4.2.2 Causes of diabetic foot
				4.2.3 Risk factors for diabetic foot
				4.2.4 Clinical manifestations of diabetic foot
				4.2.5 Prevention of diabetic foot
				4.2.6 Diagnosis of diabetic foot
				4.2.7 Self-examination of foot at home
				4.2.8 Daily foot care
				4.2.9 Foot massage and exercises
				4.2.10 Nail care and footwear selection
				4.2.11 Seeking medical help
				4.2.12 Blood glucose management
				4.2.13 Nutrition management for diabetes
				4.2.14 Medication management
				4.2.15 Insulin injection
				4.2.16 Physical exercise
				4.2.17 Psychological adjustment
	Practice for Change	After discharge, once a week	Keep a record WeChat contact	5.1 Keep a record on *Foot Care Diary Card*
				5.2 WeChat reminder
	Changes in the Social Environment	After discharge	Family support Social support	6.1 Family engagement: WeChat group for collaborative foot care.
				6.2 WeChat consultation.
				6.3 Home visit: foot examination and foot care education.

### Practice for change

Regarding “Practice for change”, a *Foot Care Diary Card* will be designed and distribute to the patients to record their performance of each specific foot care behavior every day, and the research team will be responsible for contacting the participants through WeChat to improve adherence to intervention protocols. There will be a clear instruction on the card teaching the patients daily foot care behaviors, including inspecting feet, washing and drying feet, applying lotion to their feet, foot massage, and foot exercises. The patients will receive a weekly follow-up telephone call or WeChat reminder from the nurses encouraging them to adhere to foot care practices.

### Changes in the social environment

“Changes in the social environment” will be developed by tele-nursing and home visits. After discharge, the family members, friends or the primary caregivers will be invited to join in the WeChat communication group, and they could consult the doctors and nurses in the group. In addition, the researcher nurse will also provide some information regarding foot care for them via WeChat. Tele-nursing support is available throughout the 4-week intervention and follow-up. Additional home visits will be provided if required.

In order to ensure the consistent delivery of the program, we will develop a program training for research nurses. Table 1 shows the overview of the foot-care education program.

### Patient and public involvement

During the design of this study, patient input was sought to improve the program. Three target patients reviewed the initial draft. Their perspectives on the feasibility and burden of study procedures helped to finalize the protocol.

### Data collection and management

Following randomization, baseline data will be collected via researcher-administered questionnaires, physical examinations, and biochemical tests. To ensure data quality at this stage, research nurses will check completed questionnaires for completeness immediately after collection.

A key strategy to promote participant retention and complete follow-up involves maintaining regular contact. Participants will receive reminder calls or messages prior to each follow-up assessment. Additionally, we will offer flexible scheduling for follow-up visits and express appreciation for their continued participation. For participants who discontinue the assigned intervention, we will seek their permission to continue collecting some outcome data from their medical records to enable an intention-to-treat analysis.

All paper-based forms will be transcribed into a dedicated electronic database. A comprehensive data management plan will be implemented to ensure data integrity and security. This will include double-data entry for key variables to minimize errors, along with automated range checks for data values to identify outliers. The final dataset will be anonymized and stored on a secure, password-protected computer with regular backups, accessible only to authorized research personnel.

To ensure the validity of the trial and the safety of participants, all patients are allowed to continue their regular diabetic management and must seek immediate care for any acute foot problems. However, participants are not permitted to join other structured foot care programs or trials throughout the duration of this study. The use of newly prescribed specialized footwear for ulcer prevention is prohibited unless it is deemed medically necessary, in which case it must be documented. All such concurrent care is recorded to evaluate its potential impact on the outcomes.

The results will be submitted for publication in peer-reviewed international journals and presented at relevant conferences.

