### Participants and eligibility criteria

The study will recruit diabetic patients at risk of foot ulceration from a hospital setting. Participants must meet the World Health Organization diagnostic criteria for DM [27] and the risk criteria outlined in the Guidelines for the Diagnosis and Treatment of Diabetic Foot [28,29]. The inclusion criteria will be as follows: a) diagnosis of DM without an active foot ulcer, presenting with diabetic peripheral neuropathy (DPN), with or without foot deformity, peripheral artery disease, or a history of foot ulceration or amputation; b) age ≥ 18 years; c) possession and functional use of a smartphone with WeChat by both patient and caregiver; d) absence of communication-impairing conditions (e.g., hearing loss, aphasia, unconsciousness, psychiatric disorders); and e) provision of written informed consent. Exclusion criteria will include: a) severe concomitant conditions (renal impairment ≥ stage IV, cardiac function ≥ class III, or severe cerebrovascular disease); b) pregnancy or gestational diabetes; c) peripheral neuropathy attributable to non-diabetic causes (e.g., severe hepatic/renal disease, nutritional deficiencies, connective tissue disorders); and d) concurrent participation in another clinical trial.

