### Primary outcome

#### Pre-hospital Delay Intention Survey (PHDI).

The PHDI scale, developed by Xu et al. [36], serves as a validated predictor of delay behavior in diabetic patients at risk of foot ulceration [37]. This instrument comprises seven items assessed on a 4-point Likert scale, yielding total scores between 7 and 28. Higher scores indicate stronger delay intentions. The scale demonstrates good internal consistency, with a Cronbach’s α of 0.884 [36].

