### Blood glucose

Glycemic control parameters will be prospectively collected through standardized clinical procedures. Venous blood samples will be obtained after a minimum eight-hour fast to measure fasting blood glucose (FBG), postprandial blood glucose (PBG), and glycated hemoglobin (HbA1c) through biochemical analysis, with results extracted from clinical records.

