### Statistical analyses

All statistical analyses will be performed using SPSS version 27.0 (IBM Corp., Armonk, NY, USA). Continuous variables with a normal distribution will be expressed as mean and standard deviation, while those with a non-normal distribution will be presented as median and interquartile range. Categorical variables will be summarized as frequencies and percentages and compared using the chi-square test or Fisher’s exact test as appropriate.

Longitudinal changes in primary and secondary outcomes measured at baseline, one month post-intervention, and three months post-intervention will be assessed using repeated-measures analysis of variance. The raw outcome value measured at each time point will serve as the dependent variable. Group will be treated as the between-subjects factor, and time as the within-subjects factor.

For secondary outcomes, the Bonferroni method will be applied to adjust P-values for multiple comparisons to control the type I error rate. Both intention-to-treat and per-protocol analyses will be performed. For the intention-to-treat analysis, missing data will be handled using multiple imputation under the missing at random assumption, with 20 imputed datasets generated and results pooled according to Rubin’s rules. A sensitivity analysis using complete case analysis will be conducted under the missing not at random assumption to assess the stability of the findings. Statistical significance will be defined as a two-sided adjusted P-value of less than 0.05. The study flowchart is presented in Fig 2.

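### The data route named for patients who stop the programme is medical records, which cannot supply the primary questionnaire outcome that the intention-to-treat analysis needs

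*Protocol article*

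**What the plan says.** The section on data collection and management has a separate sentence for patients who stop the programme to which they were allocated: "we will seek their permission to continue collecting some outcome data from their medical records to enable an intention-to-treat analysis". Medical records are the one data source it names for them. The sentences just before describe reminders and flexible scheduling for participants in general.

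The primary outcome is PHDI: "This instrument comprises seven items assessed on a 4-point Likert scale, yielding total scores between 7 and 28". The mode of collection is given for baseline: "baseline data will be collected via researcher-administered questionnaires, physical examinations, and biochemical tests". Foot-care knowledge, self-efficacy and behaviour are also questionnaires, and the TCSS is administered by a research nurse. The article describes one set of outcomes as coming from records, namely FBG, PBG and HbA1c, measured "through biochemical analysis, with results extracted from clinical records".

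Under Statistical analyses, "Both intention-to-treat and per-protocol analyses will be performed". For the intention-to-treat analysis, missing values are filled by multiple imputation assuming missing at random (20 datasets, Rubin's rules). The sensitivity analysis is complete-case and is labelled as being under missing not at random. The main model is a repeated-measures analysis of variance over baseline, T1 and the three-month T2.

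**The concern.** The stated means does not reach the stated end. Records are offered as what makes intention-to-treat possible, yet a routine record would not normally hold a PHDI score, nor the other questionnaire scores. Nothing else in the article says that patients who stop the programme are asked for PHDI at T1 or T2.

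At stake is what the intention-to-treat estimate describes. If no PHDI is observed after patients leave the programme, their imputed values can only be informed by patients who stayed. Under an arm-specific model, stoppers in the intervention arm are then given values as though they had continued, and the estimate moves towards an on-programme effect. The planned sensitivity analysis would not reveal this.

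**Working it through.** **1. Can the named source supply each outcome?**

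| Outcome | How the article says it is obtained | Available from records as described? |
|---|---|---|
| PHDI (primary) | Seven-item questionnaire | No |
| ADKnowl, DSES and NAFF foot-care scores | Questionnaires | No |
| TCSS | Administered by a research nurse | No |
| FBG, PBG, HbA1c | Extracted from clinical records | Yes |
| Blood pressure, weight | Measured by research nurses | Not stated |
| DFU occurrence | Assessed in the study, documented at T2 | Not stated; records could plausibly help |

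**2. Who would lack PHDI, and when?** Baseline is observed for everyone.
- Stops before T1: no PHDI at T1 or T2.
- Stops between T1 and T2: PHDI observed at T1, none at T2.

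**3. What do the planned analyses do with these patients?** Multiple imputation under missing at random predicts their values from observed data, which include no off-programme PHDI. Complete-case analysis excludes them. Neither uses a value that departs from missing at random, so the label on the sensitivity analysis does not match what it does.

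**4. The plan's own figures.** From the sample size section: d = 0.80, two-sided alpha 0.05, power 0.85. The two-sample t-test calculation gives 29.05, rounded up to 30 per group, as stated. For 15% attrition, 30 × 1.15 = 34.5, rounded up to the stated 35 (dividing instead, 30/0.85 = 35.3, gives 36). The sample size is not in dispute here.

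**5. Illustration of size.** Assumptions, none of them from the documents:
- a proportion p of the intervention arm stops before T1;
- stoppers keep a fraction k of the benefit;
- stopping in the control arm leaves PHDI unchanged;
- imputation is within arm and treats stoppers like those who stayed;
- the SD is unchanged.

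Effect in all randomised patients = 0.80 × [(1 − p) + p × k]. Imputation targets 0.80. Overstatement = 0.80 × p × (1 − k).

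The value p = 0.15 is borrowed from the attrition allowance, about 5 of 35 patients (0.15 × 35 = 5.25).

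| p | k = 0.5: effect | Overstatement | k = 0: effect | Overstatement |
|---|---|---|---|---|
| 5% | 0.78 | 0.02 | 0.76 | 0.04 |
| 15% | 0.74 | 0.06 | 0.68 | 0.12 |
| 25% | 0.70 | 0.10 | 0.60 | 0.20 |

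At p = 15%, relative to the effect in all randomised patients, this is 0.06/0.74 = 8% with half the benefit kept and 0.12/0.68 = 18% with none kept.

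**The case against.** **The article does not say that records are the only source.** The reminders and flexible visits are offered to participants generally, so the records sentence can be read as a fallback for those who no longer attend. The ethics section also keeps a patient whose sessions are paused for an ulcer in the intention-to-treat analysis, with weekly follow-up. This is fair: restriction to records is an inference from their being the sole source named for discontinuers. But neither place says that PHDI is collected from these patients, and the sentence that addresses them ties intention-to-treat to records.

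**A reader might infer that every discontinuer has no primary outcome at all, or that intention-to-treat is impossible.** The documents support neither. Baseline PHDI is observed, T1 PHDI is observed for anyone who stops after T1, and an analysis of all randomised patients can be run by imputation. T2 is also described as supplementary and outside the primary trial framework, although it enters the repeated-measures model.

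**A reader might infer that the bias certainly favours the intervention.** That is not established. The imputation model is not given and may properly sit in an analysis plan that is not shown. A model that omitted group could pull the estimate towards no effect. Higher discontinuation in the intervention arm is plausible given the diary and weekly contacts, but no figure supports it.

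**A reader might take the 0.12 SD (18%) figure as the expected bias.** It is near the unfavourable end for a 15% rate. The 15% is attrition during follow-up, not programme discontinuation, and includes people whom extra calls would not reach. Full loss of benefit is also severe: the dialogue on the harms of delay, the lecture with teach-back, the supplies and the simulation all come before discharge, so a patient who drops the later tasks has already received much of the relevant content.

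What remains is the mismatch between the named source and the primary outcome, and the absence of any statement that closes it.

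**Conclusion.** The point holds as a defect in the stated data-collection rule. The source named for discontinuers cannot provide PHDI or the other questionnaire scores. As written, PHDI after discontinuation (T1 and T2 for early stoppers, T2 for later ones) would rest on a missing-at-random assumption that the planned sensitivity analysis does not test.

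Overstatement of the effect is conditional on arm-specific imputation and on some loss of benefit after stopping. Under those assumptions, with 15% of the intervention arm stopping, it is 0.06 SD with half the benefit kept (0.74 against 0.80) and 0.12 SD with none kept (0.68 against 0.80). These are illustrations; the documents give no discontinuation rate. The sample size need not change on this account. The correction should be made before recruitment, because questionnaires not collected at T1 and T2 cannot be recovered later.

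**What to change.** Replace the sentence on discontinuers with a rule along these lines:

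- Stopping the programme does not end follow-up.
- PHDI is sought at T1 and T2 from all randomised patients, whatever their adherence, unless they withdraw from follow-up. The other questionnaires are sought if the patient is willing.
- Patients who cannot attend may answer by telephone or WeChat, and the mode of collection is recorded.
- Values collected after stopping are used in the intention-to-treat analysis.
- Medical records remain a supplement for clinical measures, including DFU occurrence.

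The cost is a few extra calls or messages for a seven-item questionnaire. The means already exist: eligibility requires "possession and functional use of a smartphone with WeChat by both patient and caregiver", and both arms have planned contact after discharge (monthly calls under routine care, weekly calls or messages in the intervention group). The downside is a possible mode difference for patients who answer remotely, which is why the mode should be recorded. Some patients will still be unreachable, so imputation remains necessary, but for fewer values and with some off-programme data to inform it.
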